## 3. Materials and Methods

### 3.1. Design and Sample

We embrace both quantitative and qualitative methods in this study. For the former, we use a case–control design comparable to the ex post facto prospective simple design with one independent variable (presence of disorder). For the latter, we explore the themes used by participants in their cognitive conflicts using the content analysis of their personal constructs. Using the sample size calculation program GRANMO v.7.12 (Institut Municipal d’Investigació Mèdica, Barcelona, Spain), we found that by accepting an alpha error of 0.05 and a beta error of 0.2 in a two-sided test, 78 subjects are necessary in each group to detect a small effect size between clinical and control groups, assuming a standard deviation of 1. The clinical sample will be formed by participants diagnosed with BPD receiving treatment from outpatient or inpatient public and private mental health facilities in the local area of Barcelona, Spain (CSMA *Germanes Hospitalàries*, ITA-*especialistas en salud mental*, and *ITLímit*). At the time of the first assessment, participants will be undergoing treatment as usual in each respective center, which will at least include individual psychotherapy. Non-specific or specific BPD group therapy, such as DBT or MBT, will also be part of therapeutic program of some participants. Regarding the qualitative line of this project, a content analysis system will be employed for the personal constructs of each participant, with special attention to those constructs that take part in cognitive conflicts.

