#### 3.2.4. Repertory Grid Technique (RGT)

The repertory grid technique is a personalized procedure using a structured interview designed to make explicit personal constructs that interviewees use to interpret and organize their interpersonal world [23,24]. It begins by identifying significant family and friends (here termed elements) and then the patient is asked to compare them (including “self now” and “ideal self”) in pairs in order to elicit the constructs used to differentiate among these elements. Once the interviewee offers a verbal tag to describe an element (e.g., “active”), they are asked to utter the opposed meaning (e.g., “passive”) to complete the bipolar dimension represented by the personal construct. Finally, the patient is asked to rate each relevant person of their interpersonal world (in addition to their actual and ideal selves) according to each personal construct expressed using a seven-point Likert scale. This creates a data matrix of elements with constructs which can be analyzed to extract several cognitive indices.

As previously mentioned, one of the main measures the RGT can provide is cognitive conflict, through the identification of implicative dilemmas and dilemmatic constructs. In order to detect the presence of implicative dilemmas, first we need to identify both congruent and discrepant constructs. The former ones are defined by the congruence between the scores of the “self now” and “ideal self” elements in that construct (e.g., being a “protector” in the example of Feixas et al. [36]), and the latter by a dissonance (or dissimilarity) between these two elements, indicating a discrepancy in the way individuals perceive themselves and how they would desire to be (e.g., not “loving herself” but wishing to do it, in the same case example). An implicative dilemma is detected when a correlation between the scores of a congruent construct and a discrepant construct is found, when the direction that the desired change indicated by the discrepant construct is associated with the loss of congruence for the self (e.g., “loving herself” is associated with being “unemotional”, the opposite pole of being a “protector”). Therefore, discrepant constructs per se do not define a conflict or dilemma but are just a discrepancy (see other measures below), a target for change. 

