#### 3.2.7. Category System to Code Personal Constructs (CSPC)

The Category System to Code Personal Constructs (CSPC) coding system has been designed within our research group and has been used in different studies in English (e.g., [36]) and Spanish to code the personal constructs elicited in the RGT in six content areas broken down into 45 categories. Feixas et al. [42] found a high reliability index for the CSPC (K = 0.93).

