### 3.4. Data Analysis

All data collected with the RGT will be analyzed with the program GRIDCOR 6.0 (Universitat de Barcelona, Barcelona, Spain), [43] to obtain relevant cognitive indexes, including cognitive conflict indicators. All measures derived from the RGT along with the rest of the quantitative information obtained by the rest of the instruments will be introduced and statistically analyzed with SPSS v.26 (IBM, Armnok, USA).

In order to prove the first two hypotheses, chi-square tests and variance analyses will be performed to determine whether there exist differences between groups regarding the presence, number and intensity of cognitive conflicts and, secondarily, other measures derived from the RGT. According to the obtained results, a logistic regression will be conducted to determine the capacity of the studied variables to predict group allocation. In the previous tests, and depending on the variations found between samples, relevant sociodemographic and clinical variables will be statistically controlled.

Considering only the clinical sample, correlations and analysis of variance will be performed to study the relations between cognitive variables (i.e., number and intensity of cognitive conflicts) and the clinical variables such as those retrieved from CORE-OM, DASS-21 and DIB-R scales and SCID-II BPD diagnostic criteria type and amount. Linear regression may be conducted depending on these results to assess the capacity of the studied cognitive conflict variables to predict progress one year later. In addition, based on the variability found in the sample, other variables will be statistically controlled. The study of predictive capacity of the variables with respect to treatment outcome one year later will be approached using regressions.

For the content analysis, two investigators will encode the personal constructs obtained with the RGT following the CSPC in the BPD sample. Differences in the content between congruent and discrepant constructs will be explored using chi-square tests.

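### The plain chi-square tests of congruent versus discrepant construct content ignore that each patient supplies several constructs, so the p-values of this exploratory analysis are not valid in general and tend to be too small

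*Protocol article*

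**What the plan says.** Section 3.4 (Data Analysis) of the protocol article fixes both the unit that is coded and the test. On coding: "two investigators will encode the personal constructs obtained with the RGT following the CSPC in the BPD sample". On testing: "Differences in the content between congruent and discrepant constructs will be explored using chi-square tests". It mentions no patient-level summary, stratification by patient or cluster adjustment for this comparison.

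Three other places bear on it:
- Section 3.1 (Design and Sample): "a content analysis system will be employed for the personal constructs of each participant". Each participant therefore contributes constructs in the plural.
- Section 3.2.4 (Repertory Grid Technique): the ratings of one person form one grid, "This creates a data matrix of elements with constructs which can be analyzed to extract several cognitive indices". To find implicative dilemmas, "first we need to identify both congruent and discrepant constructs", and this is done by comparing that same person's actual-self and ideal-self ratings.
- Section 3.2.7 (Category System to Code Personal Constructs): constructs are coded "in six content areas broken down into 45 categories".

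Section 2 (Objectives and Hypothesis) lists conflict content as a specific objective and treats it as exploratory. None of the four stated expectations concerns it.

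**The concern.** The Pearson chi-square reference distribution holds when every count in the table is an independent observation. Here the counts are constructs, and constructs come in sets from the same person. A patient may return to the same theme several times and may have many or few discrepant constructs. The plain test counts each such construct as a separate piece of evidence.

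The study's own reasoning makes patient-specific content likely. The Introduction and Discussion stress conflicts that are idiosyncratic to each patient, and section 3.2.4 treats self-ideal discrepancy as a measure on which individuals differ. If the test is too liberal, a difference in themes between congruent and discrepant constructs could be reported as typical of the BPD sample when it reflects chance clustering in some patients.

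**Working it through.** **The plan's own figure.** The document gives no number for the content analysis, so there is none to reproduce. The 78 per group in section 3.1 belongs to the comparison of patients with controls. It is used here only as the assumed number of patients.

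**Inputs.** From the documents: 78 patients, six content areas, both construct types from one grid. Assumed, because the documents do not say: m = 15 constructs per patient; 30% discrepant on average; within-patient correlation of content ρ = 0.10; between-patient correlation of the discrepant share τ = 0, 0.1 or 0.2. There is no average difference in content between construct types, so every rejection is a false positive.

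**Step 1: critical value.** A 2 × 6 table has 5 degrees of freedom, and the 5% critical value is 11.07. If clustering multiplies the variance of the contrast by V, the actual rejection rate is approximately P(χ²₅ > 11.07 / V).

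**Step 2: one theme profile per patient, shared by both construct types.** The patient's own profile largely cancels because it enters both rows. The variance multiplier reduces to V = 1 + (m − 1)τρ.
- τ = 0: V = 1, rejection 5.0%.
- τ = 0.1: V = 1 + 14 × 0.1 × 0.10 = 1.14; 11.07 / 1.14 = 9.71; rejection 8.4%.
- τ = 0.2: V = 1 + 14 × 0.2 × 0.10 = 1.28; 11.07 / 1.28 = 8.65; rejection 12.4%.

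**Step 3: theme profile also differs by construct type within a patient.** The cancellation is lost. As the extreme case, take independent profiles for the two types. Expected constructs per patient are 15 × 0.3 = 4.5 discrepant and 10.5 congruent. With τ = 0 the variance of the discrepant count is 15 × 0.3 × 0.7 = 3.15.
- Size-weighted cluster size, discrepant: (3.15 + 4.5²) / 4.5 = 5.2, so the design effect is 1 + 4.2 × 0.10 = 1.42.
- Size-weighted cluster size, congruent: (3.15 + 10.5²) / 10.5 = 10.8, so the design effect is 1 + 9.8 × 0.10 = 1.98.
- V = 0.7 × 1.42 + 0.3 × 1.98 = 1.588; 11.07 / 1.588 = 6.97; rejection 22.3%.
- τ = 0.2: the count variance is 3.15 × (1 + 14 × 0.2) = 11.97, the design effects are 1.616 and 2.064, V = 1.750, rejection 27.6%.

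**Step 4: simulation of the same settings** (2000 runs each, pooled 2 × 6 chi-square at 5%, ρ = 0.10, m = 15):

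| Discrepant share, τ | Shared profile | Type-specific profile |
|---|---|---|
| 0 | 5.1% | 21.9% |
| 0.1 | 8.8% | 25.4% |
| 0.2 | 12.6% | 28.4% |

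The simulation agrees with the formulas. With no content clustering (ρ = 0) the test stayed at about 4% to 6%.

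**Step 5: sensitivity.** With 10 to 25 constructs per patient and ρ from 0.05 to 0.20, rejection runs from about 6% to 32% for a shared profile with varying share, and from about 10% to 69% for type-specific profiles. A further simulation with 78 patients and 15 constructs gave 4% to 5% when only overall themes varied and 8% to 27% otherwise. In it a patient-clustered robust test stayed at about 4% to 7%.

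**Step 6: do within-patient permutations help?** Where only the discrepant share varied, yes: 9% for the chi-square against 4% for permutation. Where type-specific content varied between patients, no: 8.7% against 9.2%, 17.8% against 15.7%, and 18.5% against 19.5% in three settings. The permutation null is no association within any patient, which is a different hypothesis from no average difference.

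**The case against.** The strongest reply is that pooling is not stated. The article gives one sentence, says nothing about table layout, and condenses a fuller document. That is fair as far as it goes: pooling is the natural reading, not an explicit statement. But the article does name the coded unit, the compared unit and the test. The obvious alternative, a yes/no per patient for each content area, does not rescue a plain chi-square, because the same patients would appear under both construct types and the data would be paired. This is a named method that misfits the data, not a detail left out.

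Second, much of the clustering cancels because both construct types come from the same patient. This stands. A reader might infer that the p-values are wrong whatever the data look like; the check does not support that. If patients differ only in overall themes and have equal discrepant shares, the error rate stays near 5%.

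Third, the analysis is exploratory. This also stands and limits the severity. It does not make the reference distribution fit.

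Other stronger readings are tempting but unsupported:
- That patients with larger grids dominate the table: the article gives no grid sizes, and the simulations held the size constant across patients.
- That 45 separate tests will multiply false leads: section 3.2.7 describes the coding scheme, and section 3.4 does not say at which level tests will be run.
- That a future dilemma-focused module would be built on these themes: the Conclusions tie that step to the presence and number of conflicts, their association with severity and their influence on outcome, not to this test.

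**Conclusion.** The point holds as a minor one. The planned chi-square tests assume an independence that the grid design does not provide, so their p-values are not valid in general and tend to be too small. At a nominal 5% level, false rejection is near 5% if only overall themes differ between patients. It is roughly 8% to 27% if the discrepant share or the type-specific content varies as well. These figures rest on an assumed 78 patients with 15 constructs each, six content areas and moderate clustering. The documents state neither the number of constructs per patient nor the within-patient correlation, so the true size cannot be fixed from them.

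The consequence is confined to the exploratory content objective. The four hypotheses on presence, number, association with symptoms and prediction of outcome do not use this test and are untouched.

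**What to change.** Keep the category coding as planned and change only the test. In section 3.4, state that the construct is the unit of observation and the patient is the cluster. Then compare congruent and discrepant constructs on the six content areas in one of two ways:
- a logistic model for each area fitted by GEE, with patient as cluster and robust standard errors. Under an independence working structure the point estimate is the pooled contrast, and only its standard error changes;
- a chi-square with a Rao-Scott-type adjustment for clustering by patient.

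Report the 45 categories descriptively, and report the number of constructs and the discrepant share per patient so that readers can judge the clustering.

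Do not rely on a within-patient permutation test alone, for the reason shown in the working. A model with only a patient random intercept has a similar gap, because it leaves between-patient variation in type-specific content unmodelled.

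The cost is slightly more analysis work and somewhat wider intervals. GEE can be fitted in SPSS, which the article already names. Sample, coding and data collection do not change.

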## 2. Objectives and Hypothesis

The central aim of this research is to assess cognitive conflicts in individuals with a diagnosis of BPD to determine their role in the explanatory model of this disorder. These findings would permit the consideration of adapting a dilemma-focused intervention module for these patients. In addition, it would be interesting to explore other characteristics of the construction of self and others that are assessed with the RGT. The specific objectives of this study are:To verify the hypothesis that patients with BPD present more cognitive conflicts (i.e., implicative dilemmas and dilemmatic constructs) than a sample from the general population.To explore the content of cognitive conflicts in patients with BPD.To examine if the presence and number of cognitive conflicts are associated with severity of emotional symptoms in BPD patients.To test whether the presence and number of cognitive conflicts has any capacity to predict treatment outcome (in terms of psychological distress and BPD symptomatology).To explore the relevance of other aspects of the construction of self and others to explain the psychological functioning of patients with a BPD diagnosis.

It is expected that:The percentage of participants with implicative dilemmas and/or dilemmatic constructs will be superior in the group of patients diagnosed with BPD compared to a control group (community sample).The number of implicative dilemmas and/or dilemmatic constructs will be higher in the BPD group than in the control group.The presence and higher number of cognitive conflicts will be associated with greater levels of general distress clinical symptomatology (such as depression, anxiety, etc.).The presence and higher number of cognitive conflicts will predict poor treatment outcome one year after the initial assessment.

For exploratory purposes, we will also study the content of implicative dilemmas and dilemmatic constructs, and the differences with the control group regarding self-construction measures (self-ideal discrepancy, self-others discrepancy, ideal-others discrepancy) and other characteristics of the construction system (differentiation and polarization) and its association with other clinical and sociodemographic measures.

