“Rather, it is the conflictive association between a discrepant and a congruent construct which causes conflict. In these cases, the need for change (she wants to love herself) might be hindered by the need for self-ideal congruency (continue being protective). What an implicative dilemma tells us is that the need for change expressed by the discrepant construct is in conflict with the need for coherence expressed by the congruent construct. Thus, the patient unwittingly hesitates in taking a clear course of action because striving for loving herself has negative implications for her identity. In the view of such a dilemma, change may be less likely to occur because abandoning the symptoms would result in invalidation of core aspects of the self.” [36] (p. 372)

On the other hand, dilemmatic constructs are detected when the patient does not have a preference for neither pole of a personal construct and therefore indicates a middle point in the rating for the ideal self. In this situation, the individual may have doubts regarding the best position they could take in a specific personal construct, thus experiencing another type of dilemma in a construct for which each pole might involve both positive and negative implications for the self. Examples of implicative dilemmas and dilemmatic constructs can be found in Feixas et al. [36] and Paz et al. [37]. 

Other than these types of cognitive conflicts, the analysis of the RGT data matrix provides the following measures:Self-discrepancies: These measures are calculated through Euclidean distances between the elements “self now”, “ideal self” and “others” (considered as the mean of all elements other than the selves).

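### The one content comparison named in the analysis section, congruent versus discrepant constructs, cannot show which content is characteristic of cognitive conflicts

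*Protocol article*

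**What the plan says.** Section 2 lists as a specific objective "To explore the content of cognitive conflicts in patients with BPD". The same section identifies conflicts with two things, implicative dilemmas and dilemmatic constructs, and its exploratory paragraph repeats that "we will also study the content of implicative dilemmas and dilemmatic constructs".

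Section 3.1 describes a qualitative arm. Each participant's constructs are coded for content, "with special attention to those constructs that take part in cognitive conflicts".

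Section 3.2.4 gives the definitions:
- Congruent and discrepant constructs are told apart by whether the ratings of the present self and the ideal self agree.
- The section warns that "discrepant constructs per se do not define a conflict or dilemma but are just a discrepancy".
- In a quotation taken from a published case example, it adds that "it is the conflictive association between a discrepant and a congruent construct which causes conflict".
- A dilemmatic construct is one on which the patient prefers neither pole and so "indicates a middle point in the rating for the ideal self".

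Section 3.4 has two investigators code the BPD sample's constructs with the category system of Section 3.2.7 (six content areas, 45 categories). It then names one comparison: "Differences in the content between congruent and discrepant constructs will be explored", with chi-square tests. It does not say whether this is limited to constructs within dilemmas, and it does not mention dilemmatic constructs in connection with content.

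**The concern.** The objective asks about the content of conflicts, but the named comparison sorts constructs by a property that does not tell whether they belong to a conflict. A clear difference between congruent and discrepant constructs could then be reported, or read, as a finding about conflict content when it concerns self-ideal agreement. A null result could be taken to mean that conflicts have no characteristic content when that question was never tested.

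The content of each patient's own conflicts also matters to the article's argument. Its Discussion faults existing approaches for relying on conflicts derived from theory rather than on those of the individual patient. A comparison that does not isolate those conflicts contributes little to that argument.

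**Working it through.** The plan gives no figure on this point, so the check sets the definitions beside the comparison.

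**Step 1. Sort the constructs by the Section 3.2.4 definitions.** Two separate properties matter for implicative dilemmas: role (congruent or discrepant) and membership (in at least one dilemma, or in none).

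| | In an implicative dilemma | In none |
|---|---|---|
| Congruent | A | B |
| Discrepant | C | D |

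Dilemmatic constructs, call them E, are defined on another axis: the ideal self at the midpoint of the seven-point scale, which is (1 + 7)/2 = 4.

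**Step 2. Place the named comparison in this table.** As worded, it sets A and B together against C and D together. Every implicative dilemma contributes one construct to each side. E has no category of its own. The article does not say whether such constructs are left out or fall into one of the two groups.

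**Step 3. See what it estimates.** For one content area, let p with subscript A to D be the share of constructs in that cell that belong to the area. Let w be the fraction of congruent constructs that lie in a dilemma, and v the same fraction for discrepant constructs. The comparison estimates

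[w·p_A + (1 − w)·p_B] − [v·p_C + (1 − v)·p_D].

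The quantities that bear on conflict content are p_A − p_B and p_C − p_D. Two cases show that the comparison does not track them:
- If p_A = p_B and p_C = p_D, membership has no relation to content. The comparison still equals p_A − p_C, which need not be zero.
- If p_A = p_C, p_B = p_D and w = v, the comparison is zero, however far p_A lies from p_B.

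**Step 4. Try the narrower reading.** Suppose Section 3.4 means only constructs within dilemmas. The comparison is then p_A − p_C. This is informative about the two sides of a dilemma, but B and D have dropped out, so there is no reference outside conflict. E is still absent.

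**Step 5. Unit of analysis.** Each patient contributes several constructs. An ordinary chi-square over constructs treats them as independent. This is secondary here, but any replacement comparison should allow for it.

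**The case against.** The strongest reply is that the objective is exploratory and already has a method. Section 3.1 sets up a content analysis of the themes in participants' conflicts, none of the four stated expectations concerns content, and a qualitative aim needs no significance test. Section 3.4 never says that the chi-square is the answer to the objective. This stands. A reader might infer that the objective has no method, or that it would be answered by the wrong comparison; the article supports neither.

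A second reply is that congruent and discrepant constructs are the two components of every implicative dilemma, so comparing them is relevant, and that Section 3.4 does not say that all constructs enter. This stands in part. The scope is unstated, and a condensed article may leave such detail to a fuller plan. But Step 4 shows that the narrower reading still lacks a reference outside conflict and still omits dilemmatic constructs.

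Two further inferences are tempting and should be resisted:
- That the article says neither kind of construct is a conflict. It says so outright only of discrepant constructs. For congruent ones it follows from placing the conflict in the association between the two.
- That the case for a dilemma-focused module depends on this test. By the Conclusions, that case rests on the presence and number of conflicts, their link with severity and their influence on outcome.

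**Conclusion.** The point holds as a mismatch between an exploratory aim and the single comparison named for it. Whichever way its scope is read, the comparison does not contrast conflict with non-conflict content, and it gives no category to one of the two conflict types. It therefore cannot show which content is characteristic of conflicts.

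The size is modest. The descriptive content analysis remains, the hypotheses on presence, number, severity and outcome are untouched, and nothing is lost in the data. The conclusion rests on the definitions in Section 3.2.4 and on the assumption that the sentence in Section 3.4 names the planned content comparison in full. A fuller analysis plan, if one exists, may already specify more; in that case the article's sentence should be brought into line with it.

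**What to change.** In Section 3.4, name as the main exploratory content comparisons:
- **(a)** constructs that take part in at least one implicative dilemma versus those in none, done separately within the congruent and the discrepant role (A versus B, and C versus D);
- **(b)** dilemmatic versus non-dilemmatic constructs, with a statement of how dilemmatic constructs are handled in (a).

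Run these on the six content areas rather than the 45 categories: a two-group table then has 6 − 1 = 5 degrees of freedom instead of 45 − 1 = 44, and fewer sparse cells. Allow for several constructs per patient, for example with a model that treats the patient as a cluster or a test stratified by patient. Keep congruent versus discrepant as a descriptive contrast, and state that it will not be interpreted as conflict content.

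The cost is a few sentences and three comparisons (two under (a), one under (b)) in addition to the present one. They should be labelled exploratory. No new data are needed: the constructs of the BPD sample are to be coded in any case, and Section 3.4 says that the grid software yields the conflict indicators.
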